### Component 3: structure and process evaluation of OPEN AOS

#### Design

Component 3 uses a qualitative design and will involve conducting focus groups and semi-structured interviews to better explore and understand contextual factors influencing implementation, and potential scale and spread of the OPEN AOS model. Factors impacting implementation, scale and spread have been adapted from the PRISM framework and include elements such as the organisation and patients’ perspectives of the intervention; characteristics of the patients and the organisation; the external environment; and infrastructure to support implementation and sustainability [59].

### Participants

Four groups will be invited to participate in this qualitative component:

11.OPEN AOS staff members (*n* ≤ 20). Participants will be currently employed by MNHHS and have worked in the OPEN AOS model for at least 6 months.12.Older adults living in RACF and/or their family members who have received care from the OPEN AOS team (*n* ≤ 20). Participants will have had personal experience or family member experience of their relative being cared for by the OPEN AOS team within the six weeks preceding the interview.13.Staff from Queensland Ambulance Service, local Residential Aged Care District Assessment and Referral (RADAR) teams, RACFs and GPs who have referred patients to the OPEN AOS team (*n* ≤ 20).14.Executive and management stakeholders (*n* ≤ 10). Senior decision-makers involved in policy, funding, collaboration or service design related to OPEN AOS and referrers to OPEN AOS.

Participants will be invited via the following methods:

Emails will be sent to local RADAR, OPEN AOS staff and executive stakeholders via the OPEN AOS Nursing Director and/or Clinical Director. A research team member will attend RADAR and OPEN AOS staff meetings to advertise the study and invite participation.QAS will facilitate the invitation of ambulance staff including management and ambulance officers via their usual email channels. Interested staff members will be invited to contact the research team at which time they will be provided an information sheet and consent form.An email will be sent to the GP’s of RACF residents who received care from the OPEN AOS to advertise and invite them to participate in the study.RACF residents and/or their attending family members will be invited by the treating clinician at the conclusion of an OPEN AOS intervention, and asked if they would like to be contacted by the research team for more information about the study. Residents with cognitive impairment will be identified by research staff through review of clinical notes or on discussion with next of kin. The participant will have their Enduring Power of Attorney contacted and a dual consent process will occur to ensure understanding of the risks and benefits of participation.

All interested individuals will be provided with an information sheet and consent form. Invited individuals will be provided the opportunity to ask and have questions answered before written consent is obtained and the interview or focus group is conducted. Convenience sampling will be used to obtain information-rich cases from older adults who have experienced the OPEN AOS model. Some participants may be invited to take part in both a focus group and a semi-structured interview. This dual participation is intended to enhance data richness by capturing both collective perspectives and individual experiences. Participation in both activities is voluntary, and specific participants will be informed that they may choose to participate in one or both. We will predominantly conduct focus groups for participants in similar roles or within teams, and semi-structured interviews for patients and families to ensure privacy and comfort. Semi-structured interviews will also be used for GPs and executives for easier access and scheduling (up to 70 participants in total). A detailed description of the planned qualitative data collection methods is provided in Additional file 3.

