## Study design

This pragmatic multi-methods study comprises three discrete but related components: concurrent retrospective quantitative data collection for Components 1 and 2, and prospective qualitative data collection for Component 3. The approach to quantitative and qualitative data collection enables a comprehensive examination of the model’s effectiveness and real-world application. Given the multi-methods design, integration of quantitative and qualitative data through triangulation will not be undertaken. The design is underpinned by the integrated Practical, Robust, Implementation and Sustainability Model (PRISM) and Reach, Effectiveness, Adoption, Implementation and Maintenance (RE-AIM) framework [45]. PRISM will support the identification and description of contextual factors impacting RE-AIM outcomes [45]. This study has been reviewed and approved by the Metro North Human Research Ethics Committee (HREC) B (ECOO168), approval number 102,923. Data storage, retention and disposal will be conducted in accordance with the National Health and Medical Research Council (NHMRC) guidelines [46].

Three components are planned to address the following research questions:

*Component 1*

To what extent (if any) do patient characteristics (such as age, sex, and diagnostic classification^6^) and outcomes differ between OPEN AOS care and standard care (i.e. ambulance attendance with transport to ED care)?Specifically:

4.Primary Outcome: Time to be seen by treating clinician, defined as the amount of time in minutes from the initial contact with QAS to the time seen by either (i) the OPEN AOS clinician (intervention group) or (ii) the ED medical officer (control group).5.Secondary Outcomes:6.Length of care episode, defined as the amount of time in hours from initial contact with QAS to discharge of care.7.Ambulance transport to ED care: defined as the proportion of OPEN AOS patients requiring transport to ED for definitive care.8.ED re-presentation for any cause within 48 h and 28 days of discharge.9.Death within 48 h of discharge.10.Clinical incident^7^ [47] data, defined as clinical incidents that are reported by MNHHS staff that occur within 48 h of discharge.

*Component 2*

Compared to standard care, what is the incremental cost (saving) per person of the OPEN AOS model? 

*Component 3*

How do contextual factors influence implementation and potential future scale and spread of the OPEN AOS model?

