### Data collection

Semi-structured interviews will be scheduled according to participant preference, with options for in-person or online participation. Similarly, focus groups will be arranged at times and in formats that maximise participation, offering both in-person and online attendance. All semi-structured interviews and focus groups will be audio-recorded. Participants will be invited to respond to semi-structured questions guided by an a priori system for categorising qualitative data proposed by Bogdan and Biklen [60]. These a priori categories will be adapted from the PRISM framework [44] and shaped by the contextual characteristics relevant to the evaluation of the OPEN AOS model. Registered nurses recruited specifically as research assistants and the lead investigator who are not OPEN AOS clinicians will conduct the semi-structured interviews and focus groups to minimise bias. An iterative approach will be adopted, with earlier interviews shaping edits to the interview guide for later interviews. If participant distress is noted, the interviewer will ask if they wish to cease the interview or focus group and will provide a pamphlet on appropriate services to contact for assistance.

Recorded interviews and focus groups will be transcribed and anonymised prior to analysis. To achieve data saturation, data collection will continue until no new themes relevant to the study emerge from successive interviews. This will be achieved through ongoing data analyses [61]. Based on prior literature [62], we anticipate saturation may occur within approximately 12 interviews for a relatively homogeneous participant group; however, final sample size will be guided by the principle of saturation rather than a predetermined number.

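### Component 3 names convenience sampling for an aim that needs purposive selection, and sets no minimum for residents transported to ED or re-presenting after OPEN AOS care

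*Protocol article*

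**What the plan says.** Component 3 of the protocol article recruits four groups, "up to 70 participants in total". Residents and their families form one group, capped at 20.

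- **Sampling method** (Participants): "Convenience sampling will be used to obtain information-rich cases from older adults who have experienced the OPEN AOS model".
- **Route of entry** (Participants): residents or attending relatives "will be invited by the treating clinician at the conclusion of an OPEN AOS intervention" and asked whether the research team may contact them. The episode of care must fall in the six weeks before the interview.
- **Stopping rule** (Data collection): "data collection will continue until no new themes relevant to the study emerge from successive interviews".
- **Expected size** (Data collection): "we anticipate saturation may occur within approximately 12 interviews for a relatively homogeneous participant group", with saturation, not a fixed number, deciding the final size.

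These sections give no selection criterion, stratum or minimum number for residents by what happened to them. They exclude nobody on that ground either. Anyone treated by OPEN AOS within the six weeks is eligible, including those later taken to hospital. The Limitations section accepts that recruitment may favour people who are easier to reach or better disposed to the service, and proposes no change to the sampling in response.

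**The concern.** The method and the aim in one sentence do not match. Convenience sampling selects on availability. An information-rich case is one chosen because of what it can tell, which requires a criterion.

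Three other stated rules add to the problem.

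- The service's own clinician makes the invitation. It comes at a moment when re-presentation within 48 h or 28 days, both Component 1 outcomes, cannot yet be known.
- A run of similar, uncomplicated cases can satisfy a rule of no new themes. Saturation would then describe the people reached and not the range of experience.
- The group is small.

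Component 3 is meant to inform delivery, scale and spread. Accounts from residents and families for whom care in the facility did not suffice bear directly on that. Under the rules as written, the resident and family group may contain none.

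**Working it through.** **Inputs from the protocol article**

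- Group caps (Participants): 20, 20, 20 and 10.
- Resident and family group: at most 20.
- Anticipated saturation: about 12 interviews (Data collection).
- Transport to ED after OPEN AOS care: a Component 1 secondary outcome, "defined as the proportion of OPEN AOS patients requiring transport to ED for definitive care". No rate is given anywhere.

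**Reproducing the plan's own figure.** 20 + 20 + 20 + 10 = 70, which agrees with the stated total.

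**Chance that the group contains no transported case.** Let p be the proportion transported among those interviewed and n the number of interviews, with one case per interview and cases independent. Then P(none) = (1 − p)^n. As p is not given, it is assumed to lie between 5% and 30%.

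Examples: 0.95^12 = 0.54 and 0.70^12 = 0.014; 0.95^20 = 0.36 and 0.70^20 = 0.001.

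**Allowing for uneven recruitment.** If transported cases are only half as likely to be recruited (an assumption), replace p by p′ = 0.5p / (0.5p + 1 − p). For p = 0.10, p′ = 0.05 / 0.95 = 0.053. Then P(none) = 0.947^12 = 0.52 and 0.947^20 = 0.34.

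| Assumed p | n = 12, proportional | n = 20, proportional | n = 12, half as likely | n = 20, half as likely |
|---|---|---|---|---|
| 5% | 54% | 36% | 73% | 60% |
| 10% | 28% | 12% | 52% | 34% |
| 15% | 14% | 4% | 36% | 18% |
| 20% | 7% | 1.2% | 24% | 10% |
| 30% | 1.4% | 0.1% | 10% | 2% |

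**What the table does and does not show.** The proportional columns would be the same for a simple random sample. They measure the effect of small n with no minimum, not the effect of convenience sampling. The right-hand columns show what selective recruitment could add, but the factor of one half is illustrative. If a resident and a relative both count towards the cap for one episode, the number of distinct cases is below n and the risk is higher.

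**Whether later re-presenters can be reached.** The eligibility window is 6 × 7 = 42 days and the longer re-presentation outcome is 28 days. That leaves 42 − 28 = 14 days in which to interview someone whose 28-day status is known.

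**Search effort.** If p applies to willing families, one transported case turns up on average in every 1/p of them: 20 at 5%, 10 at 10%, and 3.3 at 30%.

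**The case against.** The strongest reply has four parts.

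- **The rate is unknown.** At 20% or more, with proportional recruitment and 20 interviews, the chance of missing every transported case is about 1% or less. This stands. A reader might infer that the sample will probably, or easily, miss such cases. The documents do not support that, because the answer depends on a rate they do not give.
- **The bias is disclosed and other sources exist.** The Limitations section names it. Ambulance staff, facility staff and GPs can describe episodes that ended in transport, the Rigour section plans triangulation across groups, and Component 1 counts transports and re-presentations. This lowers the stakes. It does not supply the resident and family view, which is one of the listed factors in the framework, and the four groups are analysed separately before being contrasted.
- **Additional file 3 is not shown.** It describes the qualitative data collection and may hold more detail. The absence of quotas from an article would not by itself be a finding. The article, however, states the method outright. If the file sets purposive criteria, the sentence in the article is wrong and needs correcting.
- **Component 3 asks about context, not frequency.** That is true, and it is a reason to seek variety of experience, not a reason to take whoever is available.

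Three further inferences should not be drawn.

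- The staff rule ("Participants will be currently employed by MNHHS and have worked in the OPEN AOS model for at least 6 months") does not clearly shut out everyone who has left the service. Someone who completed six months and moved elsewhere within MNHHS appears eligible.
- Residents with cognitive impairment are not left out by design, as the Participants section gives them an identification step and a dual consent process.
- 735 × 6/52 ≈ 85 is not a firm count of candidates in any six-week window. It carries 2022–23 volume into a prospective component and counts patients treated, not people willing to be interviewed.

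**Conclusion.** The point holds in a limited form. The article names a sampling method that does not deliver the aim stated in the same sentence. Together with clinician invitation, the cap and the stopping rule, nothing assures that the resident and family group includes anyone transported or re-presenting.

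The size is uncertain. Under an assumed transport rate of 5% to 30%, proportional recruitment and one independent case per interview, the chance of none is 54% to 1.4% at 12 interviews and 36% to 0.1% at 20. It is higher if such cases are less readily recruited. Because a random sample of equal size would do no better, the missing element is the minimum and not randomness.

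This is a minor but worthwhile improvement. It leaves the Component 1 and Component 2 analyses untouched.

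**What to change.** In Component 3, Participants, replace convenience sampling of residents and families with purposive maximum-variation sampling within the same cap of 20.

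- Set a small target minimum for transported or re-presenting residents and another for those who stayed home. Where feasible, do the same for telehealth and in-person care.
- Keep the clinician's invitation as the route to consent for contact, and let the research team choose whom to interview from those who agree. Time some interviews after day 28 but within the six weeks, so that re-presentation is known.
- In Data collection, add that saturation is not declared for this group until the minimums are met or the cap is reached, and that any shortfall is reported.

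The cost is a change of wording, possibly a minor ethics notification, and somewhat slower recruitment, more so if transport is rare. No additional participants are needed. If convenience sampling is kept, delete the claim that it yields information-rich cases.

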### Data collection

Semi-structured interviews will be scheduled according to participant preference, with options for in-person or online participation. Similarly, focus groups will be arranged at times and in formats that maximise participation, offering both in-person and online attendance. All semi-structured interviews and focus groups will be audio-recorded. Participants will be invited to respond to semi-structured questions guided by an a priori system for categorising qualitative data proposed by Bogdan and Biklen [60]. These a priori categories will be adapted from the PRISM framework [44] and shaped by the contextual characteristics relevant to the evaluation of the OPEN AOS model. Registered nurses recruited specifically as research assistants and the lead investigator who are not OPEN AOS clinicians will conduct the semi-structured interviews and focus groups to minimise bias. An iterative approach will be adopted, with earlier interviews shaping edits to the interview guide for later interviews. If participant distress is noted, the interviewer will ask if they wish to cease the interview or focus group and will provide a pamphlet on appropriate services to contact for assistance.

Recorded interviews and focus groups will be transcribed and anonymised prior to analysis. To achieve data saturation, data collection will continue until no new themes relevant to the study emerge from successive interviews. This will be achieved through ongoing data analyses [61]. Based on prior literature [62], we anticipate saturation may occur within approximately 12 interviews for a relatively homogeneous participant group; however, final sample size will be guided by the principle of saturation rather than a predetermined number.

### Data analysis

The qualitative data will be analysed using thematic analysis, following the six-step approach described by Braun and Clarke [63] and informed by a priori categorisation to guide the coding process whilst remaining open to inductive codes. This will ensure that interview and focus group transcripts are analysed in alignment to the research question based on PRISM domains [44]. Transcripts of interviews and focus groups will be read and re-read with initial tags assigned to sections of text to familiarise the researchers with the data. Using a priori labels provides a separate accounting scheme for the deductive analysis of qualitative data by limiting analysis to focus on contextual characteristics experienced by participants relevant to the OPEN AOS model. The data collected from the four groups of interviewees will be analysed separately to compare and contrast findings [60]. NVivo will be used to manage and organise the transcribed interview data and coding system, supporting systematic coding, retrieval and comparison. Component 3 will follow the Consolidated criteria for reporting qualitative research (COREQ) reporting guideline for qualitative research [64].

### Rigour

To ensure the trustworthiness and credibility of findings in Component 3, several strategies aligned with Lincoln and Guba’s (1985) framework for qualitative rigour will be implemented [62]. First, the standardisation of coding through use of a priori categories will provide a consistent framework for analysing data. Additionally, three research team members will code the data independently and discuss preliminary findings with the research team, debating any differences and agreeing by consensus. This approach enhances the reliability and dependability of the analysis. To minimise bias, the interviewers will use a reflexive approach, adhere to a structured interview guide, and avoid influencing participant responses. To ensure transferability we will include sufficient descriptive data such as verbatim quotes, to offer rich contextual insights, allowing readers to assess the applicability of findings to other contexts. Finally, triangulation of data by incorporating multiple perspectives from the OPEN AOS team, referrers and patients and/or their carers will strengthen credibility and minimize potential bias.

## Discussion

The increase in patient volumes and more diverse emergency care needs of communities have seen a need to shift from traditional ED designs to designs better able to address safety, quality, and patient experience expectations [65]. Further shifts have occurred and a recent (2024) systematic review on strategies for improving ED-related outcomes of older adults has concluded that efforts to improve older patients’ needs should focus on interventions initiated outside the ED [66]. Novel models of care have and continue to emerge that utilise alternative care pathways to reduce unnecessary ambulance transport to hospital, ED investigations and interventions. The OPEN AOS model represents an innovative ED substitution approach, whereby person-centred emergency care is delivered to older adults living in RACFs.

### Limitations

This study is subject to several methodological limitations. First, the findings should be interpreted in the context of the limitations inherent to non-randomised comparisons. Without random allocation, there is an increased risk of selection bias, baseline differences, and unmeasured confounders that may influence observed outcomes. These factors limit the ability to draw causal inferences and should be considered when evaluating the study’s conclusions. We envisage that findings from this study will inform a future randomised controlled trial. Second, the recruitment strategy may have introduced recruitment bias. The approaches adopted may favour individuals who were more engaged with organisational communication channels, more available, or more positively oriented toward the service, potentially underrepresenting those with differing experiences or lower levels of engagement.

### Future implications

This study will provide ED clinicians and policy makers with evidence on the impact, translatability and cost efficiency of the OPEN AOS model within one hospital and health service in South-East Queensland, Australia. Findings will inform local model refinements and guide future resource allocation decisions. Importantly, this evidence will add to the body of knowledge regarding emergency care for older vulnerable adults residing in RACFs. This study will provide valuable information regarding this emergency outreach model’s capacity to deliver timely care and reduce unnecessary transport of older adults to ED. Furthermore, the identification of barriers and enablers to implement and scale effective emergency substitution models can guide future endeavours to strengthen emergency care for older adults.

Findings from this study have the potential to inform national and international frameworks aimed at improving access to and quality of emergency care for older adults. These insights may guide adaptation of similar models in other jurisdictions and support the development of patient-centred approaches to emergency care for vulnerable older populations. As the global community adapts to an aging population, continued efforts to optimise care for older adults in their place of residence through the use of alternative care options (such as OPEN AOS) are required.

